# **3 Selection and Withdrawal of Subjects**

## **3.1 Inclusion Criteria**

*This section should contain details of age, sex, disease, prior treatment constraints etc., under which a subject is deemed to be suitable (eligible) to participate in the trial. This also includes healthy volunteers and any “control”*

*groups etc. Each such “group” should be defined separately. Informed consent to participate (preferably written and witnessed) must be stated as an inclusion criterion. A simple list format is the preferred style.*

- i. aged 2 to 15 years with
- ii. chronic kidney disease with stages 1-4 the last 12 months and
- iii. with or without anti-hypertensive/s medications (irrespective of recent change/s in anti-hypertensive therapy). Subjects on anti-hypertensive medications must be able to tolerate either an ACEi or ARB's.
- iv. subjects with average clinic systolic BP <50th percentile and on no antihypertensive medication will be eligible as 'CONTROL' subjects only
- v. other 'CONTROL' subjects will include children with normal renal function and blood pressure attending hospital for unrelated medical review or siblings of subjects with CKD

## **3.2 Exclusion Criteria**

*This section should contain details of age, sex, disease, prior treatment constraints etc., under which a subject is considered to be unsuitable for inclusion into the study population. (Examples frequently include exposure to prior radiotherapy in cancer trials, and participation in a trial with an investigational product within the previous three months in pharmacokinetics trials). A simple list format is the preferred style.*

- i. age <2 and >15 years
- ii. subjects who have/had an arterio-venous fistulae,
- iii. subjects who have/had are on dialysis
- iv. subjects who have/had a functioning kidney transplant
- v. patients with symptomatic BP or with past history of difficulty to control BP or
- vi. patients in whom there is a clinical urgency to treat BP and inclusion in study may result in possible delay of treatment
- vii. patients with arrhythmia or clinical heart failure
- viii. patients with known structural cardiac abnormality
- ix. subjects on treatment with angiotensin converting enzyme inhibitor (ACEi) or angiotensin receptor blocker (ARB) agents for treatment of proteinuria only or
- x. subjects who are likely to be of clinical concern following up or down titration of BP levels as described in 'Appendix 3'
- xi. subjects who are unable or intolerant to performance of study measurements e.g. height, echo or PWV
- xii. subjects who have/had intolerance to Angiotensin converting enzyme inhibitors (ACEi) and ARB's drug/s or have any existing contraindications

## **3.3 Withdrawal of Subjects**

*Please provide details of when and how to withdraw subjects from the trial or investigational product treatment. It is essential that you specify the type and timing of the data to be collected for withdrawn subjects and indicate whether (and if so, how) withdrawn subjects are to be replaced, as well as arrangements for safety assessment follow-up of any subjects withdrawn from the trial as a result of (Serious) Adverse Events.*

- i. Subjects will be withdrawn if they are unable to tolerate the performance of study related measurements e.g. height, echo or PWV or if they develop concerning adverse effects as a result of ACEi/ ARB's class of anti-hypertensive drug/s used as part of taking part in the study.
- ii. If a subject wishes to withdraw from the study this will be allowed. Identifiable data already collected with consent would be retained and used in the study. No further data or tissue would be collected or any other research procedures carried out on or in relation to the participant.

- iii. In principle we would aim to keep blood and urine specimen and data gathered up to the point that the consent is lost. However as the patients are continually followed up by the clinical team we will be able to determine if the patient wants us to withdraw their data from the study. We will always follow the patient and/or their families wishes.

## **4 Assessment of Efficacy**

### **4.1 Efficacy Parameters**

*Describe the measures that will be used to determine the efficacy of treatment (eg glucose, blood pressure, tumour reduction etc). Primary efficacy parameters should be stated first, then any secondary parameters and “surrogate markers” listed in 4.1.2.*

#### **4.1.1 Primary Efficacy Parameters**

N/A

#### **4.1.2 Secondary Efficacy Parameters**

N/A

### **4.2 Procedures for Assessing Efficacy Parameters**

*Describe here the procedures for determining the primary (and secondary) efficacy parameters (eg venepuncture, 25 mls to be drawn 12 hrs post treatment for full blood count, SMAC and glucose, or CT scan at 6 months, etc). State also here what is to be recorded in the CRF (eg WBC, Hb, Urea, Glucose etc rather than “FBC” or “SMAC”) – ie stipulate the parameters that are actually to be used for the analysis of efficacy. (See also Safety Parameters, 5.1 below)*

N/A

## **5 Assessment of Safety**

### **5.1 Specification, Timing and Recording of Safety Parameters.**

*Describe the measures that will be used to determine subject safety during the study. These will include physical examination, blood tests and adverse event reporting. Obviously, there will be close correlation with efficacy testing intervals and efficacy blood tests etc. In this section the tests that to be performed for assessing the safety of the subject should be appropriate to the treatment (eg WBC and platelets in chemotherapy, LFTs if there is a known or suspected risk of hepatotoxicity, U&Es if there is a risk of renal problems etc), although “general” assessments from FBC or SMAC would be acceptable. As with efficacy measures, please stipulate (ie repeat even if given above) the times at which safety evaluations will be conducted (Please do not write “see above” in this section; please copy & paste from 4.2 as and where appropriate).*

All subjects will have clinic BP maintained in the assigned target range over the duration of the study. Up or down titration of blood pressure during the trial will be performed as per flowcharts in **Appendix 3**. Amendments to the 'BP titration' procedures (appendix 3) will be made if necessary following review of data after 20 subjects.

Adverse events will be assessed at each study visit.

Important expected adverse events will be actively surveyed (i.e. must be assessed to complete the case report form).

An independent Data Monitoring Committee (DMC) will review adverse event data annually or more frequently if requested by the DMC.

## 5.2 Procedures for Recording and Reporting Adverse Events

Investigators will assess the seriousness and causality (relatedness) of all AEs experienced by the patient. Definitions of different types of AE are listed below.

**Adverse Events (AEs):** An adverse event is any untoward medical occurrence in a subject as a result of taking part in the research study (study medication, application of the study device) or within a previously specified period of time after the treatment has been completed. An AE can therefore be any unfavourable and unintended sign (including an abnormal laboratory finding), symptom or disease temporally associated with the use of medication as part of taking part in the study. As the safety profiles of the anti-hypertensive agent/s used in this trial are well described, only Adverse Reactions (ARs) experienced during treatment will be reported. Pre-existing condition/s, diagnostic and therapeutic procedures, such as surgery (although the medical condition for which the procedure was performed must be reported if new) performed in the routine management of the subjects condition are not defined as AE. Any worsening of any pre-existing condition/s will be reported.

**Adverse Reactions (ARs)** An AR is an AE if judged as having a reasonable causal relationship to the anti-hypertensive agent/s. This usually means that there is evidence or argument to suggest a causal relationship.

**Serious Adverse Events (SAEs):** An SAE is any AE that: (i) Results in death; (ii) Is life threatening (an event in which the patient was at risk of death at the time of event); (iii) Requires in-patient hospitalisation or prolongation of existing hospitalization; (iv) Results in persistent or significant disability or incapacity; (v) Results in a congenital anomaly or a birth defect (vi) Or is otherwise considered medically significant by the Investigator.

Important AEs that are not immediately life threatening or do not result in death or hospitalisation but may harm the subject or may require intervention to prevent one of the other outcomes listed above, should be considered serious.

The following SAEs do not require immediate reporting by the site and are not regarded as unexpected for the purpose of this trial. Events not considered SAEs are any period of hospitalizations for (i) Routine treatment/ monitoring of the condition, not associated with any deterioration in condition and (ii) Treatment, which was elective or pre-planned, for a pre-existing condition that is unrelated to the indication under study, and has not worsened.

Expected SAEs are those listed in the current IB of the used anti-hypertensive agent/s. These are available at <http://emc.medicines.org.uk/>. Further information about anti-hypertensive agents can also be obtained at <http://www.bnf.org/bnf/index.htm>

**Serious Adverse Reactions (SARs):** A SAR is an SAE if a reasonable causal relationship can be made to the anti-hypertensive agent. This usually means that there is evidence or argument to suggest a causal relationship. Factors to consider when assessing causality of SARs include the nature and timing of the reaction and its relationship to the dose of the anti-hypertensive medication.

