#### **Reporting all Types of Adverse Events**

##### **1. Reporting Adverse Events/Reactions**

Adverse events relating to the patients underlying disease and its treatment will be assessed at each study visit, and recorded on the follow-up data collection form. The study investigators will provide details of all adverse events to the Data Monitoring Committee (DMC) for their review on an annual basis.

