#### 1.5 Method of allocation of groups

After informed consent was obtained and eligibility confirmed, participants were randomised by the chief investigator using a rapid, secure, web-based randomisation system developed by the Kings Clinical Trial Unit, London. Randomisation to standard or intensive treatment arms (1:1) was stratified according to clinical centre.

In this open-label multi-centre trial participants and recruiting clinicians were informed of the participant's allocation and trial related systolic BP targets electronically. Therefore, no unblinding or code breaking is required. Further, those performing investigations were blind to participants SBP percentile and target, and the trial team and recruiters blinded to results.

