### **2.3 Adverse event reporting**

Adverse events and serious adverse events will be summarised by treatment arm.

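### For non-serious events the protocol reports only reactions that a doctor attributes to an antihypertensive drug. This conflicts with its other safety rules and leaves the SAP's by-arm adverse event table undefined.

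*Combined protocol and SAP*

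**What the plan says.** **The reporting rule.** Protocol 5.2 argues that the safety of the drugs is already well known, and concludes that "only Adverse Reactions (ARs) experienced during treatment will be reported". It then says "An AR is an AE if judged as having a reasonable causal relationship to the anti-hypertensive agent/s".

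**The definition of an adverse event (AE).** The same section opens causally: "An adverse event is any untoward medical occurrence in a subject as a result of taking part in the research study". The next sentence is temporal and extends to any "symptom or disease temporally associated with the use of medication as part of taking part in the study". A serious adverse event (SAE) is an AE that meets a seriousness criterion.

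**The design.** SAP 1.4 randomises children with or without antihypertensives to a target. SAP 1.5 says "In this open-label multi-centre trial participants and recruiting clinicians were informed of" the allocation and the systolic target. Protocol 5.2 has a doctor judge causality, against the antihypertensive or concomitant therapy.

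**The analysis.** SAP 2.3 is one sentence: "Adverse events and serious adverse events will be summarised by treatment arm". It does not say whether all AEs or only ARs are meant.

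**The concern.** The stated reason for the AR-only rule is that the drugs are familiar. The question under test is whether holding children with CKD at a lower pressure is beneficial and acceptable, and the documents do not claim that the safety of that target is already known.

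Harm from a target need not look like a drug reaction. It may come from the pressure level itself or, in the other arm, from pressure left higher. Neither fits a definition that asks whether the drug caused the event, and a child on no antihypertensive cannot have an AR at all.

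If the AR-only sentence governs, the non-serious part of the by-arm table mixes true harm with two other quantities: who was on a drug, and how readily a doctor who may know the allocation blamed it. If the wider rules govern, the table means something else. A reader of the SAP cannot tell which.

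**Working it through.** The plan states no figure on this point, so the check is mainly a comparison of its own rules.

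**Step 1. What each rule captures**

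| Place | Events covered | Causality needed? |
|---|---|---|
| Protocol 5.2, AE paragraph | ARs during treatment only | Yes, to the drug |
| Protocol 5.2, end of the same paragraph | Deterioration of a condition the child already had | No |
| Protocol 5.1 | AEs asked about at every study visit; important expected ones actively sought | No |
| Protocol 5.2, Reporting Adverse Events/Reactions | AEs of the disease and its treatment recorded at visits; every AE passed to the DMC yearly | No |
| Protocol 5.2, Reporting Serious Adverse Events/Reactions | Every SAE, within 24 hours | No; causality is one of five items collected |
| Protocol 5.2, end of the SUSAR paragraph | Remaining SAEs, from the start of protocol treatment to three months after the last treatment | No |
| SAP 2.3 | AEs and SAEs by arm | Not stated |

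For non-serious events the first row cannot be followed together with rows two to four. For serious events the rows agree that causality is not a filter.

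**Step 2. A concrete clash.** Table S3 lists a fall in glomerular function under ACEi/ARB intolerance (5 intensive, 2 standard) and eGFR below 15 under its own heading (3 and 3). These are withdrawals, not AE counts, but they show that renal decline can be assigned to drug or disease. A non-serious decline assigned to disease is not reportable under the AR-only sentence, yet is reportable as deterioration of an existing condition.

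**Step 3. Children on no drug.** Tables S1 and S2 allow a rough estimate of their share at baseline: (overall mean − treated mean) / (untreated mean − treated mean).

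- LVM: overall (70.1×64 + 74.0×60)/124 = 71.99; (71.99 − 69.1)/(77.6 − 69.1) = 0.340
- LVMI: overall (31.9×64 + 30.3×60)/124 = 31.13; (31.13 − 30.4)/(32.5 − 30.4) = 0.346
- LVM z-score, using the Figure S6 baseline means: overall (−1.13×64 − 1.28×60)/124 = −1.203; (−1.203 + 1.29)/(−1.03 + 1.29) = 0.336
- RWT: overall (0.34×64 + 0.36×60)/124 = 0.3497; (0.3497 − 0.34)/(0.36 − 0.34) = 0.48, from heavily rounded inputs

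Three rows point to about 0.34 × 124 = 42 children. The fourth shows how rough the method is. It establishes only that the untreated group was not trivial at entry. It says nothing about exposure by arm during follow-up. The targets themselves can make exposure differ: an untreated child between the 50th and 75th percentiles is at target in one arm and above it in the other.

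**Step 4. How the count behaves under the AR-only rule.** For events that are not deterioration of an existing condition:

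reported risk = true risk × share on drug × probability of attribution

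The documents give no attribution rates, so the following are assumptions. With equal exposure and a true risk of 0.20 in both arms:

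- attribution 50% v 50%: 0.10 v 0.10, ratio 1.00
- attribution 50% v 40%: 0.10 v 0.08, ratio 1.25; reversed, 0.80
- attribution 50% v 30%: 0.10 v 0.06, ratio 1.67; reversed, 0.60

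A real excess can also vanish. True risks of 0.30 v 0.20 with attribution of 30% v 45% give 0.30×0.30 = 0.09 and 0.20×0.45 = 0.09. This shows that the mechanism can work in either direction. It does not estimate what happened.

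**The case against.** The strongest reply is that the protocol as a whole is wider than one sentence. Events are asked about at each visit, the DMC receives all of them, and the AR-only sentence could be read as governing onward reporting rather than recording. Every AE is also to be assessed for causality, which would make little sense if only causally related events counted. This stands in part: the documents do not prove that non-serious events were filtered. But the reply works only by setting the sentence aside. With 14 recruiting centres (Table S4), sites could reasonably have followed different rules.

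Four stronger readings are tempting and are not supported:

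- **That SAEs are filtered by causality too.** A reader might infer this because an SAE is built on the AE definition. The SAE rules say otherwise, and a serious adverse reaction is defined separately as an SAE with a causal link. What remains is an ambiguity. The phrase "any untoward medical occurrence in a subject as a result of taking part in the research study" and a window tied to protocol treatment leave it unclear whether a child on no drug is covered.
- **That the AE definition simply requires a causal link.** Its second sentence is temporal. Both sentences, however, are tied to participation or medication.
- **That SAP 2.3 is the only safety comparison.** Progression of renal failure is a secondary objective (SAP 1.1), and withdrawals with reasons are summarised (SAP 2.2).
- **That more reactions in the arm with more treatment would be a false excess.** Extra drug reactions from extra treatment are a genuine cost of a lower target.

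Two further limits are fair. That the assessing doctors know the allocation is inferred from the open-label design: the blinded roles named are those performing measurements and entering data, and the AE assessor's status is not stated. And SAP 2.3 plans a descriptive summary, with no test.

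**Conclusion.** The point holds for non-serious events. The AR-only sentence contradicts Protocol 5.1, two other provisions of 5.2 and the plain sense of SAP 2.3. If followed, it would omit harm that is not a drug reaction and let attribution and exposure shape the counts by arm. For SAEs the residual problem is narrower: unclear coverage of children on no antihypertensive.

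The size and direction of any distortion cannot be found from the documents, and the ratios shown rest on assumed attribution rates. A reader might conclude that the planned table would measure attribution instead of harm. That goes too far: ARs are harms, deterioration of existing conditions is reportable whatever its cause, and the wider rules may have been followed in practice. The supportable conclusion is that the table would mix harm with attribution and exposure in unknown proportions, and that the plan does not say which events it contains.

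This should be fixed. It does not affect the primary LVMI analysis.

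**What to change.** 1. **Protocol 5.1 and 5.2:** delete the AR-only sentence. Define an AE as any untoward medical occurrence in a randomised child, regardless of cause or drug exposure. Record causality as a field on the existing follow-up form.
2. **SAE window:** word it so that it clearly covers a randomised child on no antihypertensive, and reconcile it with the rule that every SAE is recorded.
3. **SAP 2.3:** summarise all AEs and all SAEs by arm regardless of causality, with ARs and serious adverse reactions as a secondary table. Give the DMC the same tables.
4. **If collection is complete:** state which rule was applied and label the table accordingly. Events never recorded cannot be recovered by a change in wording.

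The cost is a protocol and SAP text change and somewhat more event recording at visits already scheduled. In the last case it is wording only.

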#### **Suspected Unexpected Serious Adverse Reactions (SUSARs)**

A SUSAR is an SAR, which is of a type or severity which is not consistent with the up-to-date product information in IB.

Details of all other SAEs will be documented and reported from the date of commencement of protocol defined treatment until three months after the administration of the last treatment.

#### **Assessing Severity and Causality of AEs and SAEs**

All AEs and SAEs should be evaluated by a doctor to determine severity and causality between the anti-hypertensive agent/s and/or concomitant therapy and the AE.

#### **Reporting all Types of Adverse Events**

##### **1. Reporting Adverse Events/Reactions**

Adverse events relating to the patients underlying disease and its treatment will be assessed at each study visit, and recorded on the follow-up data collection form. The study investigators will provide details of all adverse events to the Data Monitoring Committee (DMC) for their review on an annual basis.

##### **2. Reporting Serious Adverse Events/Reactions**

All SAEs must be recorded on the adverse event form and faxed to the CI within 24 hours of the research staff becoming aware of the event. Please ensure that the local Principal Investigator has assigned causality and expectedness to the SAE before reporting. For each SAE, the following information will be collected: (i) Full details in medical terms with a diagnosis, if possible. (ii) Action taken (iii) Outcome (iv) Causality, in the opinion of the investigator\* and (v) Whether the event would be considered expected or unexpected\*

\*Assessment of causality and expectedness **must be made by a doctor**. If a doctor is unavailable, initial reports without causality and expectedness assessment should be submitted to the CI by a healthcare professional within 24 hours, but must be followed up by medical assessment as soon as possible thereafter.

#### **Reporting SUSARs**

SAEs classed by the local investigator as both suspected to be related to the anti-hypertensive agent/s and unexpected are SUSARs, and are subject to expedited reporting. The investigator should complete a SAE form, and fax to the CI within 24 hours of the research staff becoming aware of the event.

The Chief Investigator (or nominated individual) will undertake urgent review of SUSARs within 24 hours of the event being reported. The Chief Investigator will not overrule the causality, expectedness or seriousness assessment given by the local investigator but may comment on these and can upgrade if deemed appropriate.

#### **Data and Safety Monitoring Plan**

An independent Data Monitoring Committee (DMC) will be established for this trial and will include members as per standard guidelines and include at least one member from each of the following

designations: a statistician, an expert in renal disease and an expert in cardiovascular medicine. The DMC will meet annually to review all collected data and may meet more frequently if required after analysis of the available data. The DMC will advise the Trial Management Committee and the independent Trial Steering Committee on the safety of continuing this clinical trial.

